## STORAGE AND HANDLING OF INVESTIGATIONAL PRODUCT

Study device will be packaged, labeled, and shipped to the study site by the Alcresta Pharmaceuticals, Inc. Study device will be supplied in kits containing the required number of devices and labeled. The label on the kit includes a tear-off portion to be affixed to the subject’s source document or label page provided for this purpose.

Study device will be stored securely on site, in an area only accessible by site staff, at 15°C to 30°C. The subject’s parent or guardian will be instructed to keep the subject’s study device at room temperature: 15°C to 30°C. Parents or guardians will be instructed to return any used study devices at each clinic visit. Damaged or suspect study device will be returned unused to Alcresta. No special handling of the study device is required.

All study device supplies will be accompanied by accountability and shipping documents that will be maintained by the investigator or designee. Information recorded on these accountability and shipping documents will include relevant dates, batch numbers, quantities received or dispensed, to whom dispensed, returned device(s), and indication of device lost or damaged. Pharmacy dispensing records will be reviewed by a study monitor periodically to ensure adherence with procedures for dispensing of RELiZORB. At the end of the study, all used and unused RELiZORB will be accounted for. The remaining study device supplies will be destroyed on site.

## COMPLIANCE WITH INVESTIGATIONAL PRODUCT

The subject’s parent or guardian will be required to document the subject’s daily nutritional intake (24 hour oral and enteral caloric intake/composition and PN volume) using an electronic phone-based application (Cronometer; or paper diary if there is no electronic capability). The study device use and incidence of any changes in symptoms (e.g., abdominal pain, increases in stool output above baseline) will be recorded using the electronic diary (or paper diary). The subject’s parent or guardian will receive education and continued support from a study dietician to assist them in keeping track of nutritional and total caloric intake, as well as caloric composition in the diary throughout the duration of the study. Access to the electronic nutrition application (Cronometer) will facilitate this recording. The first and final clinic visits will be preceded by a required 72-hour stool collection for fat analysis.

The study staff will review the diaries and question the subject or the subject’s parent or guardian about protocol compliance at the clinic and weekly telephone visits. For hospitalized subjects, compliance will be assessed through daily monitoring of nutritional markers and review of medication administration records which utilize point of care bar code technology. Details of the study device use will be recorded on the CRF.

In the event that an out-of-state study patient is hospitalized at a hospital other than Boston Children’s and to ensure patients are able to remain in the study at an outside institution, at the time the patients are enrolled in the study, they will be provided a copy of their signed consent and the study protocol with study team contact information with instructions to bring these materials, along with the supply of RELiZORB devices, to the hospital so that they can use them in the event of an inpatient admission.

If a subject fails to comply with protocol requirements, the subject may be discontinued from the study. Compliance will be considered to have been achieved if the subject receives ≥80% of the planned enteral nutrition using the device.

## CONCOMITANT MEDICATIONS

Prohibited medications or therapies and restrictions for any drugs prior to receiving the open labeled study device are provided in the sections for inclusion criteria and exclusion criteria. A complete list of current medications will be ascertained at enrollment and each successive study visit.

Patients using enteral bile salt sequestering agents (e.g., cholestyramine, colestipol, colesevelam) at enrollment must continue to receive them for the duration of the 90 day study period. In patients who are not receiving these medications at enrollment, they cannot be initiated until the patient has completed the study. If a patient does start a bile salt sequestering agent during the study, they must be withdrawn from the study.

Patients will continue to receive the same lipid emulsion product throughout the study period. If a patient switches lipid emulsion products during the study period, they will be withdrawn from the study.

Patients who are using medications such as probiotics, antibiotics utilized for small intestinal bacterial overgrowth, fiber supplementation, and/or proton pump inhibitors must continue to receive them for the duration of the 90 day study period. In patients who are not receiving these medications at baseline, they cannot be initiated until the patient has completed the study. If the patient does start these medications during the study, they must be withdrawn from the study.

- 1. **INPATIENT USE**

In the event the patient does get admitted to hospital during the study period, they will be allowed to continue to use the RELiZORB device to administer their enteral nutrition. Since 2017, RELiZORB has been approved for use in Boston Children’s Hospital without any restrictions to nursing unit, patient population or clinician group. Copies of the Patient Care Manual policy and corresponding reference tool are located in the appendix.

# MANAGEMENT OF NUTRITIONAL SUPPORT DURING THE STUDY

Clinical parameters for management of pediatric short bowel syndrome will be considered for advancing nutritional support (PN/IV and/or oral/enteral feeding) in volume and calories during the 90 day study. Adjustment of nutritional support in volume and calories will be made at all planned study visits and during weekly phone calls as deemed appropriate (Figure 2). Clinical parameters to be considered include the following:

- Maintaining growth (including weight and height) by the subjects trending along their growth chart and adjusting calories/volumes to maintain the trend
- Serum electrolytes (assessed during study visits and, if needed for PN adjustment, will also be assessed in between visits)
- Increase in the Volume Intake/Output ratio, including mixed output that can be collected
- Consideration of clinical deterioration in SBS
- Weight loss
- Diarrhea (> 50 mL/kg/day with ostomy)
- Vomiting frequency
- Fluid balance
- Skin breakdown of perianal area

Adjustments will be based on the actual nutritional support in volume and calories the subject infuses. Subjects are expected to remain compliant with the nutritional support prescription in volume and calories during the study. Nutritional support constituents may be adjusted at the discretion of the investigator. During the 48-hour Intake/Output measurement period, no significant changes to nutritional support will be made. If there is a change in oral fluid intake, the investigator will consider this when adjusting the nutritional support in volume and calories.

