| This clinical trial includes an initial screening visit (Day -3) in which subjects will be screened for eligibility, including baseline clinical and physical assessments. At screening the investigator or designee will review the subject’s medical history to determine eligibility, explain the study to the subject and the subject’s parent or legal guardian, and if eligible, obtain informed consent. If consent is given and the subject is deemed eligible based on the results of the screening visit, they will be enrolled in the study and pre-baseline assessments will be performed, which will include physical examination, nutritional assessment, vital signs, 72-hour fecal stool collection, and clinical evaluations.  Treatment will be administered on study Day 1, followed by daily use of the RELiZORB enzyme cartridge whenever enteral nutrition is administered, for a total of 90 days. During the treatment period, all enteral nutrition will be administered through the RELiZORB enzyme cartridge. Nutritional intake (24-hour enteral dietary and PN volume intake), stool consistency/amount/frequency (if applicable) or ostomy (if applicable) output, study device use, and incidence of symptom changes will be recorded daily electronically or on paper by the subject’s parent or guardian. Throughout the duration of the study, parents or guardians will also be contacted daily by a study coordinator and/or dietician to assess nutritional record and identify any other potential problems. Clinic visits will occur on Days 7, 14, 28, 60, and 90 (range ± 3 days) of the treatment period. Assessments for the primary endpoint and safety will be collected during these visits and through a weekly phone call with at-home weight measurement using a standardized scale. Advancement of oral or enteral feedings and weaning from parenteral feeding will be determined by the investigator during the weekly phone calls and scheduled clinic visits based on the subject’s clinical status, which will include assessment of weight, growth and hydration status. | |
| **Number of subjects (planned):** A total of 32 pediatric subjects with SBS, aged 2 years -18 years, are expected to be enrolled in the study over a period of 48 months. | |

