# STUDY DESIGN

## BASIC DESIGN CHARACTERISTICS

This study is a phase 3, open labeled uncontrolled single center,
clinical trial to determine the safety, tolerability, and bioavailability of the RELiZORB enzyme cartridge with enteral nutrition when used daily for a total 90 days of treatment when given to pediatric subjects with SBS, aged 2 years – 18 years, who have been PN dependent for at least 6 months.

Subjects with a signed informed consent will be enrolled in the study. Results from screening must not show any clinically significant abnormalities in order for the subject to progress to the enrollment and treatment phases of the trial. During the screening visit, subjects and legal guardians will also receive education from a registered dietician on recording caloric intake and composition in oral and enteral feeds, and PN. As part of this education, the subject and parent/guardian will receive access to a nutrition/food tracking phone application (Cronometer) to assist them with this task throughout the study. If there is no electronic capability, a paper diary will be provided. The subject and parent/guardian will also receive education from a registered nurse on accurate and complete stool collection. Subjects will be provided with a standardized weight scale for at-home weight recording.

Upon completing screening and enrollment, subjects and their legal guardians will be instructed to record total calories and composition in oral and enteral feeds and TPN and to collect all stool for 72 hours (Days -3 to -1) prior to the first day of treatment. The stool collection and recording will be repeated in the 72-hours preceding the final study visit (Days 87-89). All stool will be collected in a single container and kept refrigerated during collection. If necessary (for example, out of state participants, excessively watery stools), subjects will be admitted to our dedicated research center during this collection period.

On the first day of treatment (Day 1), all subjects will use the RELiZORB enzyme cartridge to administer their enteral nutrition and will continue to use a cartridge daily for a total of 90 days. The study device will be used with enteral nutrition administered to the subject daily by a parent or guardian for 90 days (Day 1 to Day 90).

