| Clinical laboratory evaluations^d^ | X |  |  |  | X |  | X |  | X |
| Dietician Education | X |  | X |  | X |  | X |  | X |
| 72-hour fecal collection^e^ |  | X |  |  |  |  |  |  | X (final visit) |
| Lipid profile^f^ | X |  |  |  | X |  | X |  | X |
| Total plasma FAs^g^ | X |  |  |  | X |  | X |  | X |
| Liver tests^h^ | X |  |  |  | X |  | X |  | X |
| Nutritional assessment | X |  | X |  | X |  | X | Weekly | X |
| Record nutritional intake^i^ |  | Daily | X | Daily | X | Daily | X | Daily | X |
| Change in PN/ enteral feeding | X | X | X |  | X |  | X | Weekly | X |
| Home Body weight (WAZ) |  |  |  |  |  |  |  | Weekly |  |
| RELiZORB |  |  | X | Daily | X | Daily | X | Daily | X |
| Adverse Events^j^ |  |  | X | Daily | X | Daily | X | Daily | X |
| Concomitant Medications |  |  | X | Daily | X | Daily | X | Daily | X |
| Assess medical/ surgical procedures | X |  | X |  |  |  | X |  | X |
| Supply Investigational Product |  |  | X |  | X |  | X |  | X |
| Review Daily Patient Diary |  |  |  |  | X |  | X | Weekly | X |

I/E criteria = Inclusion and exclusion criteria.

FAs =fatty acids.

PN = Parenteral nutrition.

^a^ Record known bowel length/type from last surgical resection or other measurement.

^b^ Blood pressure, pulse rate, respiratory rate and temperature.

^c^ Includes height or length, head circumference (for subjects < 36 months), and weight. If a physical examination or nutrition assessment was performed during the 3-day screening period, it will be used for the baseline assessment when available.

^d^ Includes chemistry (including fat-soluble Vitamins A, D, E, and K), hematology, coagulation and C-reactive protein (CRP). Clinical laboratory evaluations obtained at time of screening will serve as the baseline assessment.

^e^ 72-hour fecal collection will occur in the 72 hours preceding treatment day 1 and the final clinic visit day 90

^f^ Samples of the lipid profile will include cholesterol, high-density lipoprotein (HDL), very low-density lipoprotein (VLDL), and low-density lipoprotein (LDL). Results of samples obtained at time of screening will be analyzed during enrollment period, prior to participant receiving device.

^g^ Samples of total plasma fatty acids will include total saturated, total monosaturated, total polyunsaturated, total Omega-3, total Omega 6, total fatty acids, a-linolenic Acid, linoleic acid, oleic acid, EPA, arachidonic acid, mead acid, DHA, and triene:tetraene ratio.

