^h^ Serum alanine aminotransferase (ALT), serum aspartate aminotransferase (AST), and serum gamma-glutamyl transpeptidase (GGT)

^i^ 24-hour nutritional intake/composition (PO and enteral dietary intake and PN volume) will be recorded using a phone-based application or paper diary. This will be especially important during the 72-hour stool collection periods for calculation of the coefficient of fat absorption.

^j^ Adverse events will be recorded daily in an electronic or paper format by the subject’s parent or guardian, and by study staff during clinic visits. Monitoring of these events will also occur through a daily phone call from a study coordinator. If any AEs or concerns are noted by the family, the study coordinator will alert the study team by email. PI or other delegated investigator will determine next steps

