### Enrollment Period (Day -3 to -1)

After completion of screening and if eligible, the subject will be enrolled in the study. During this enrollment period, the subject’s parent or guardian will be responsible for a 72-hour stool collection preceding Day 1. If necessary (for example, out of state participants, excessively watery stools), subjects will be admitted to a dedicated research center at our institution during this collection period. This stool collection will be repeated prior to the final Day of the study (Day 90).

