2. *Quantitative total fat*: The collected stool sample is sent to BCH central lab for quantitative total fecal fat measurement
   1. The coefficient of fat absorption will be calculated using the total stool mass, total fat analysis, and the following equation:

CFA= [Total Dietary fat (72 hours) – Total Stool Fat (72 hours)] ÷ Total Dietary Fat (72 hours)

1. *Stool and Plasma Fatty acid profile* :

Stool and plasma fatty acid composition will be analyzed at OmegaQuant Analytics by gas chromatography (GC) with flame ionization detection. Stool samples will be weighed into a screw-cap glass vial which contain tritricosanoin as an internal standard (tri-C23:0 TG) (NuCheck Prep, Elysian, MN), homogenized and then extracted with a modified Folch extraction. A portion of the organic layer will be transferred to a screw-cap glass vial and dried in a speed vac. After samples are dried BTM (methanol containing 14% boron trifluoride, toluene, methanol; 35:30:35 v/v/v) (Sigma-Aldrich, St. Louis, MO) is added. The vial is briefly vortexed and heated in a hot bath at 100˚C for 45 minutes. After cooling, hexane (EMD Chemicals, USA) and HPLC grade water is added, the tubes are recapped, vortexed and centrifuged help to separate layers. An aliquot of the hexane layer will be transferred to a GC vial. GC will be carried out using a GC-2010 Gas Chromatograph (Shimadzu Corporation, Columbia, MD) equipped with a SP-2560, 100-m fused silica capillary column (0.25 mm internal diameter, 0.2 um film thickness; Supelco, Bellefonte, PA).

1. Fatty acids are identified by comparison with a standard mixture of fatty acids (GLC OQ-A, NuCheck Prep, Elysian, MN) which was also used to determine individual fatty acid calibration curves. Fatty acid composition is expressed as a percent of total identified fatty acids and concentrations as µg/mg of stool.

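### The protocol's only hold on nutritional changes names an undefined 48-hour Intake/Output period, while the 72-hour fat-balance collections have no hold

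*Protocol*

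**What the plan says.** Section 5.0 allows PN and feeds to be adjusted at every planned visit and at the weekly calls. Its single restriction is "During the 48-hour Intake/Output measurement period, no significant changes to nutritional support will be made". Intake/Output is mentioned in one other place, also in Section 5.0, as a ratio to weigh when adjusting support, with no duration or timing. No 48-hour period appears in Table 2, the Section 7 procedures, the endpoints or the synopsis.

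The 72-hour collections, by contrast, are defined repeatedly. Section 4.4 states: "The first and final clinic visits will be preceded by a required 72-hour stool collection for fat analysis". Section 3.1 puts them on Days -3 to -1 and Days 87-89. For those days the plan asks that intake be recorded; Table 2 footnote i adds: "This will be especially important during the 72-hour stool collection periods for calculation of the coefficient of fat absorption". Section 7.1.6 divides dietary fat minus stool fat by dietary fat, all over the same 72 hours. No sentence asks for steady feeding during a collection.

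Two places contemplate adjustment around the baseline collection. The synopsis, under its heading for Days -3 to -1 and Day 1, has the investigator decide whether nutritional treatment should change. Table 2 marks its feeding-change row at Screening, Enrollment and Day 1 ("Change in PN/ enteral feeding | X | X | X"), then weekly in the column that includes Days 61-89. On visit timing the synopsis says: "Clinic visits will occur on Days 7, 14, 28, 60, and 90 (range ± 3 days) of the treatment period".

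**The concern.** A balance study needs intake to be steady while output is collected, and for long enough beforehand that the stool belongs to that intake. Here the one rule of this kind is attached to a period that staff cannot locate from the protocol text, and the two collections that need the rule lack it. A 48-hour hold would not fit them even if it was meant for them: it would leave 24 of 72 hours, one third, uncovered.

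At stake is the reading of change in CFA, with fecal fat alongside it. If feeds are advanced around the final collection, dietary fat rises at once and stool fat follows later. Apparent absorption goes up for a reason unrelated to the cartridge, in the direction the trial hopes to see and with no control arm to show it. The same advance in the baseline collection would understate benefit, as would a cut around the final one.

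**Working it through.** **1. Is there a hold elsewhere?** Three provisions come near:
- Section 7.1.3 says the regimen is not changed for research purposes and that subjects stay on it. This does not bar clinically driven changes.
- Section 3.2.1 (criteria 5 and 9) requires stable PN, subject to investigator discretion, and unchanged formula and rate for a month before screening. This does not cover the collection itself.
- Section 4.5 fixes the lipid emulsion product, not its amount or the feeds.

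None holds feeds steady during a collection.

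**2. Can an adjustment contact meet a collection?** Screening is Day -3, which is also the first collection day. At the end, the collection occupies the three days before the visit, and the last weekly assessment listed in Section 10.2.2 before the final one is Day 84. Day 90 is taken to be the final visit itself and to move with it.

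| Final visit | Collection | Day 84 contact |
|---|---|---|
| Day 87 | Days 84-86 | inside |
| Day 88 | Days 85-87 | one day before |
| Day 89 | Days 86-88 | two days before |
| Day 90 | Days 87-89 | three days before |
| Day 93 | Days 90-92 | six days before |

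Unscheduled visits may replace calls (Section 7.1.4), so contacts are not confined to the listed days.

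**3. Effect on CFA.** The protocol gives no change size, timing, lag or expected CFA, so all four are assumptions. Let a be true absorption, c the proportional change in total dietary fat, T the hour of change and L the stool lag, treated as a pure delay.

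Apparent CFA = 1 - (1 - a) × [72 + c(72 - T - L)] / [72 + c(72 - T)]

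Bias = (1 - a) × cL / [72 + c(72 - T)]

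Worked case, a = 0.60, c = 0.20, T = 24, L = 24: 1 - 0.40 × 76.8/81.6 = 0.6235, a bias of +2.35 points. With T = 24 throughout, in percentage points:

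| Rise | Lag | a = 0.40 | a = 0.60 | a = 0.80 |
|---|---|---|---|---|
| 10% | 12 h | 0.9 | 0.6 | 0.3 |
| 10% | 24 h | 1.9 | 1.3 | 0.6 |
| 20% | 12 h | 1.8 | 1.2 | 0.6 |
| 20% | 24 h | 3.5 | 2.4 | 1.2 |

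A 20% cut in the worked case gives 1 - 0.40 × 67.2/62.4 = 0.5692, or -3.08 points. If the protocol's 32 subjects all contribute, one child with the +2.35 bias moves the mean by 2.35/32 = 0.07 points.

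**4. Would a hold inside the window be enough?** No. If the change comes exactly at the start (T = 0), the worked case gives 1 - 0.40 × 81.6/86.4 = 0.6222, a bias of +2.22 points, which is 2.22/2.35 = 94% of the mid-window figure. For a change s hours before the start, with s no greater than L, the bias is (1 - a) × c(L - s) / [72(1 + c)]. At s = 12 this is 0.40 × 0.20 × 12/86.4 = 1.11 points; at s = 24 it is zero. The lead-in has to be at least as long as the lag.

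**5. Effect on the primary outcome.** Section 10.2.2's formula spans 83 days. A sustained 5% PN cut ordered on Day 1, after the baseline value, gives AUC7-90 = 0.950. Deferred so that it first shows at Day 14, it gives (7 × 0.975 + 76 × 0.95)/83 = 0.952. The difference is 0.002 for that child.

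**The case against.** The 48-hour period may be defined in Figure 2 or the Study Procedures Manual, neither of which is at hand, and Section 5.1 does mention caregiver measurements around visits. This stands. A reader might infer that the period does not exist; the documents show only that the visible text leaves it undefined, so the sentence should not simply be deleted. Neither possibility puts a 72-hour hold into the protocol text.

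The baseline collection is partly protected. Subjects stay on their regimen at the start, a month of stability precedes screening, and Sections 5.0 and 7.1.4 place adjustment in the treatment period. The Table 2 row sits among measurements and may mean recording. A reader might infer that changes on Days -3 to -1 are openly permitted; the text is ambiguous rather than permissive. The ambiguity remains because the synopsis has the investigator consider changes under that same heading.

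On the nominal schedule the final collection, Days 87-89, misses the listed contacts. This also stands: direct overlap with Day 84 needs the visit on Day 87. Because the bias also arises from changes just before a collection, final visits on Days 88 and 89 have some exposure too.

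Daily intake records already capture most changes, and CFA uses intake from the same window. That allows an affected child to be identified, but it does not remove the lag.

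**Conclusion.** The point holds and is minor. The protocol's one stability rule is tied to a period the visible text does not define, and the two collections behind fecal fat and CFA are left without one. For a child whose dietary fat rises by 10-20% 24 hours into a collection, apparent CFA is inflated by about 0.3 to 3.5 percentage points under the stated assumptions on lag and true absorption. How many children would be affected cannot be judged from the protocol, so no trial-level bias is claimed.

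The mechanism works through dietary fat. A PN change alone does not enter the CFA formula; PN belongs in the hold because Section 5.1 considers PN reduction and feed advancement together.

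A reader might infer that the primary result is at risk. It is not, on this ground: AUC7-90 is 0.950 against 0.952 in the example, and Section 10.2.2 already fixes the Day 1 value as the denominator. Nor does the point bear on whether open-label weaning after Day 1 can be attributed to the device.

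**What to change.** - In Section 5.0, state that no non-safety change to PN or enteral feeding is made during either 72-hour collection, or in a short lead-in before it, for example 24-48 hours. For feeds, the one-month enteral stability criterion largely covers the baseline lead-in.
- Tie the final hold to the dates on which stool is actually collected, not to Days 87-89, because the visit may move by three days either way.
- Define the 48-hour Intake/Output period and place it in Table 2. If it is a carry-over with no counterpart in this trial, replace it with the hold above.
- Mark the feeding-change row of Table 2 as recording only at Screening and Enrollment, and align the synopsis text for those days.

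The cost is protocol wording. Elective adjustments wait a few days around each collection, safety-driven changes go ahead as now, and no visit or procedure is added.
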